### **Power and Sample Size**

Through the PFC quality improvement initiative, we have found the accuracy rate of the EMR algorithm to be approximately 80%. As such, we anticipate 1,080 of 1,350 subjects will be eligible with 270 subjects enrolled on to each of the four arms in a 1:1:1:1 ratio. We estimate a base return rate for controls to be 15% and a base return rate for the intervention arms to be 25%. We will compare the intervention arms against the control arms but we will not compare one intervention against another intervention. We have 80% power to detect an absolute 10% increase in response rate using a two-sided Type 1 error rate of 0.05.

### **Data Analysis**

We will conduct a chi-square analysis using statistical software Stata 12 to compare each intervention arm to the control arm. A second chi-square analysis will be performed by blinded members of the research team to compare response rates of the study participants and patients receiving FIT as standard clinical care. Analysis will be conducted by the research team twelve weeks after the last subsample questionnaire is completed.

### **Subject Population(s) for Analysis**

The population that will be included in the primary study analysis will include subjects who were randomized into the study and who completed FIT as an intention to treat analysis. Two populations will be included in the secondary analysis. The first will include any subjects randomly selected to receive a subsample questionnaire and who completed the questionnaire. The second will include patients who currently receive FIT as standard of care in the Penn Family Care Clinic. In order to provide a comparison group, retrospective chart review will be performed on this group in order to compare response rates and demographics between study participants and the eligible clinic population. The data collected on these patients will be identical to the data collected on study participants (i.e. demographics, inclusion criteria, exclusion criteria, response rates).

**\*\*New changes from initial protocol notated in bold, parts removed from initial protocol notated in strikethrough**

### Power and Sample Size

Through the PFC quality improvement initiative, we have found the accuracy rate of the EMR algorithm to be approximately 80%. As such, we anticipate 1,080 of 1,350 subjects will be eligible **and randomized**, with 270 subjects enrolled on to each of the four arms in a 1:1:1:1 ratio. We estimate a base return rate for controls to be 15% ~~and a base return rate for the intervention arms to be 25%. We will compare the intervention arms against the control arms but we will not compare one intervention against another intervention.~~ **We will compare each intervention arm to the control and use Bonferroni correction for an alpha of .017 (.05/3) in order to account for three comparisons.** Thus, we have 80% power to detect an absolute ~~40%~~ **11 percentage point** increase in response rate using a two-sided Type 1 error rate of ~~0.05~~ **0.017**.

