### Data Analysis

We will conduct a chi-square analysis using statistical software Stata 12 to compare each intervention arm to the control arm. ~~A second chi-square analysis will be performed by blinded members of the research team to compare response rates of the study participants and patients receiving FIT as standard clinical care.~~ Analysis will be conducted by the research team twelve weeks after the last subsample questionnaire is completed.

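### Holm's step-down test would detect more effective incentives than single-step Bonferroni at the same 5% familywise error, for one sentence in the SAP

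*Supplement*

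**What the plan says.** The Power and Sample Size text is the same in the Final SAP and in section 7 of the Final Protocol. The design has four arms, "with 270 subjects enrolled on to each of the four arms in a 1:1:1:1 ratio". Every incentive arm is to be tested against control, and for multiplicity the plan will "use Bonferroni correction for an alpha of .017 (.05/3) in order to account for three comparisons". The power claim is "we have 80% power to detect an absolute" rise of "11 percentage point" size, two-sided, at 0.017, from a control return rate of 15%.

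The Data Analysis section adds only the test: "We will conduct a chi-square analysis using statistical software Stata 12 to compare each intervention arm to the control arm". Neither final document names a stepwise or ordered procedure, and neither says what confidence intervals will be reported. The rule in force is therefore one fixed threshold applied separately to each of the three p-values.

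**The concern.** Single-step Bonferroni holds every comparison to the strictest threshold, even after one or two comparisons have already succeeded. Holm relaxes it: the smallest p-value is compared with 0.05/3, the next with 0.05/2 and the last with 0.05, stopping at the first failure. Familywise control at 5% is kept without any assumption about how the tests are correlated. Any comparison significant under Bonferroni at 0.05/3 is also significant under Holm.

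What is at stake is the second and third finding. If more than one incentive works, the fixed threshold may leave an effective one undeclared where Holm would declare it, with no saving in familywise error guarantee, sample size or assumptions.

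**Working it through.** **Inputs from the Power and Sample Size section.** n = 270 per arm; control rate 0.15; detectable difference 0.11, so an incentive-arm rate of 0.26; two-sided alpha 0.017 per comparison, that is 0.05/3 = 0.01667; three comparisons with a shared control. The Data Analysis section gives the test, a chi-square, taken here without continuity correction.

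**1. The plan's own power figure.**
- Critical value at 0.017 two-sided: 2.387.
- Pooled rate: (0.15 + 0.26)/2 = 0.205. Standard error under the null: √(2 × 0.205 × 0.795/270) = 0.03475.
- Standard error under the alternative: √((0.15 × 0.85 + 0.26 × 0.74)/270) = 0.03442.
- Power, pooled: Φ((0.11 − 2.387 × 0.03475)/0.03442) = Φ(0.787) = 78.4%.
- Power, unpooled: Φ(0.11/0.03442 − 2.387) = Φ(0.809) = 79.1%.
- Difference detectable at exactly 80% (pooled): 11.2 points, which rounds to the stated 11.

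The stated 80% is reproduced to within rounding.

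**2. Validity of the planned rule.** With equal arms and one shared control, the three test statistics have correlation 0.5. Under the global null, the chance of at least one rejection at 0.017 is 4.5%, both by normal approximation and by simulation of the binomial data. Holm gives 4.4%.

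**3. Bonferroni at 0.017 against Holm at 5%.** Simulation of 1,000,000 trials per scenario, 270 per arm, control rate 15%, uncorrected chi-square, Holm thresholds 0.05/3, 0.05/2 and 0.05.

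| Incentive-arm rates | Measure | Bonferroni | Holm |
|---|---|---|---|
| 26, 26, 26% | power per arm | 78.9% | 85.4% |
| 26, 26, 26% | all three detected | 59.1% | 75.0% |
| 26, 26, 26% | at least one detected | 94.7% | 94.6% |
| 26, 26, 15% | power per effective arm | 78.9% | 81.5% |
| 26, 15, 15% | power for the effective arm | 78.8% | 78.7% |

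The gains are 85.4 − 78.9 = 6.5 points per arm and 75.0 − 59.1 = about 16 points for all three if every incentive works, and 81.5 − 78.9 = 2.6 points per arm if two work. The 0.1-point deficits arise because Holm starts at 0.05/3 and the printed Bonferroni threshold is 0.017.

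**4. What Holm costs.** With two effective arms and one ineffective arm, the ineffective arm's own false-positive rate rises from about 1.7% to between 3.8% and 3.9% (repeat runs differ slightly). Simulated familywise error for Holm did not exceed 4.4% in any scenario.

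**5. Which intervals to report.** Every extra Holm rejection has a p-value between 0.0167 and 0.05, the range in which a 98.33% interval tends to include zero. With all three arms at 26%, about 94% of the extra rejections have a 98.33% Wald interval that includes zero, and about 17% of trials show at least one such conflict. A 95% interval avoids this: with equal arms the unpooled variance never exceeds the pooled one, so a chi-square p-value of 0.05 or less goes with a 95% Wald interval that excludes zero.

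**The case against.** The best case for the plan as written is that single-step Bonferroni is prespecified, matches the power statement and controls the familywise error. It also has simultaneous intervals that agree closely with its tests, which is a legitimate reason to prefer it in a study that calls itself a pilot. The largest gain occurs in the pattern most favourable to Holm, and detecting all three incentives is not a stated objective. All of this stands. It makes the point an efficiency suggestion and limits its size, but it does not remove the gain.

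A reader might also infer more than the documents support:

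- **That rounding to .017 breaks the 5% limit.** It is true that 3 × 0.017 = 0.051. But the text prints the exact fraction beside the rounded figure, the actual familywise error is about 4.5%, and the rounding slightly adds power (78.4% against 78.2% at exactly 0.05/3). It has no practical effect and is no part of this point.
- **That the trial expects several incentives to work.** The common 25% return rate for the intervention arms is struck out of the final text. What remains is a detectable difference for each comparison, with no statement of how many arms should succeed. The scenarios above are therefore conditional.
- **That the trial misses its stated power.** The 78% to 79% agrees with 80% once the 11.2-point detectable difference is rounded to 11.

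**Conclusion.** The point holds as a cheap improvement. The planned analysis is valid, and no conclusion drawn under it would exceed its 5% familywise error. Holm would do better whenever more than one incentive works: about 79% to 85% per arm and 59% to 75% for all three if every arm has the 11-point effect, and about 79% to 81.5% per arm if two have it. It gives no gain when one arm works, nor for detecting at least one.

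These figures rest on the plan's 15% control rate, 11-point effect and 270 per arm, and on an uncorrected chi-square. How many incentives are effective is an assumption, since the documents do not say. Holm's familywise control and its superiority to Bonferroni at 0.05/3 do not depend on any of these.

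**What to change.** In the Final SAP, and in section 7 of the Final Protocol so that the two agree, state that the three comparisons with control are tested by Holm's procedure at familywise two-sided alpha 0.05, with the ordered p-values compared with 0.05/3, 0.05/2 and 0.05 in turn, stopping at the first non-significant result. Keep the existing power statement and describe it as the conservative first-step figure.

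In Data Analysis, make the Holm-adjusted p-values the decision rule. Report each risk difference with a 95% confidence interval labelled as not adjusted for multiplicity. Do not pair Holm with 98.33% intervals, which would contradict most of the extra rejections.

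The change takes a sentence on the test and a line on the intervals, with no extra subjects or data. It has two costs. The intervals are not simultaneous and not matched to the step-down test, so one may exclude zero for an arm that Holm does not declare significant; hence the label. An ineffective arm's own false-positive rate also rises (about 1.7% to 3.9% when the other two work), within the 5% limit. The change should be made before outcomes by arm are examined.

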### Data Analysis

We will conduct a chi-square analysis using statistical software Stata 12 to compare each intervention arm to the control arm. ~~A second chi-square analysis will be performed by blinded members of the research team to compare response rates of the study participants and patients receiving FIT as standard clinical care.~~ Analysis will be conducted by the research team twelve weeks after the last subsample questionnaire is completed.

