## Duration

*Subject duration:* We anticipate it taking the subject no more than 15 minutes to prepare, complete, and mail the FIT.

*Study duration:* We anticipate participant enrollment to occur in batches on a rolling basis, such that each of nine batches will include two months of chart review and sending of FIT kits. Given this in conjunction with a two-month wait period (after the last kit is mailed), and a three month analysis period, we anticipate this pilot project to last 23 months.

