## 8. Data and Safety Monitoring

### Protected Health Information/Data Protection

We will abstract the following variables from PennChart.

- Name
- Address
- Birth date
- Date of most recent CRC screening (e.g. colonoscopy, sigmoidoscopy, FOBT/FIT)

- Medical and family history
- Phone number
- Medical record number

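### The final SAP prespecifies no covariate-adjusted analysis; a standardized risk difference adjusted for batch, age and screening history would be a cheap, modest efficiency gain

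*Supplement*

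**What the plan says.** The Data Analysis section of the final SAP, and the same section of the final protocol, give one comparison: "We will conduct a chi-square analysis using statistical software Stata 12 to compare each intervention arm to the control arm". No covariate, stratified analysis, effect measure or confidence interval is named.

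Power and Sample Size in the final SAP sets the test level ("use Bonferroni correction for an alpha of .017 (.05/3) in order to account for three comparisons") and the control assumption ("We estimate a base return rate for controls to be 15" per cent), with 270 subjects per arm. The claim opens "Thus, we have 80% power to detect an absolute", gives the difference as "11 percentage point" and is completed by "increase in response rate using a two-sided Type 1 error rate of" 0.017.

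The final protocol describes three baseline factors:

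- **Batch.** Section 4, Duration, expects "participant enrollment to occur in batches on a rolling basis", in nine batches of two months each.
- **Age.** Birth date is on the chart-abstraction list in section 8, and age 50 to 75 is an inclusion criterion.
- **Screening history.** The same list includes "Date of most recent CRC screening (e.g. colonoscopy, sigmoidoscopy, FOBT/FIT". The criteria in section 5 cannot be applied without it, because they require that a patient is due and set look-back windows for colonoscopy, sigmoidoscopy and stool tests.

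The Randomization section describes a computer-generated algorithm and names no stratification factor.

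**The concern.** With a binary endpoint (kit returned within two months) and three two-arm tests at 0.017, each raw comparison leaves in the error term whatever outcome variation the baseline factors could explain. Someone who has been screened before may be more likely to return a mailed kit. Batch carries season and any change over time in who was enrolled or what was mailed. The change log dates revisions to letters and eligibility criteria in 2016, although it does not say which batches these touched. If these factors do predict return, an adjusted comparison of return rates would be more precise for the same 1,080 subjects. What is at stake is a few points of power and slightly narrower intervals. The validity of the test is not in question.

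**Working it through.** **Inputs from the final SAP.** Control rate 0.15; detectable difference 0.11, so 0.26 in an incentive arm; n = 270 per arm; two-sided alpha 0.017, so z = 2.387.

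**Step 1: the plan's own power figure.** Using the pooled variance under the null and the unpooled variance under the alternative:

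- mean rate = (0.15 + 0.26)/2 = 0.205
- null SE = √(2 × 0.205 × 0.795/270) = 0.03474
- alternative SE = √((0.15 × 0.85 + 0.26 × 0.74)/270) = 0.03442
- power = Φ((0.11 − 2.387 × 0.03474)/0.03442) = Φ(0.786) = 78.4%

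Taking alpha as exactly 0.05/3 gives 78.2%; unpooled variance throughout gives 79.1%. The difference detectable with 80% power is 11.2 points, which rounds to the stated 11.

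**Step 2: effect of adjustment on the risk-difference scale.** If the covariates explain a share R² of outcome variance, the variance of the standardized risk difference shrinks by about (1 − R²). This is equivalent to n = 270/(1 − R²) per arm. The documents give no R², so a range is shown.

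| Assumed R² | Equivalent n per arm | Power, 15% vs 26% | Detectable difference at 80% power (points) |
|---|---|---|---|
| 0 | 270.0 | 78.4% | 11.2 |
| 0.02 | 275.5 | 79.4% | 11.1 |
| 0.05 | 284.2 | 80.8% | 10.9 |
| 0.10 | 300.0 | 83.1% | 10.6 |

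**Step 3: what an R² of 0.05 would require.** As an illustration only, suppose 40% have prior screening on record and return at 25%, and the other 60% return at 8.33%. Overall: 0.4 × 0.25 + 0.6 × 0.0833 = 0.15. Then R² = 0.4 × 0.6 × (0.1667)²/(0.15 × 0.85) = 0.0067/0.1275 = 0.052. That is worth 270/(1 − 0.052) − 270, or about 15 subjects per arm.

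**Step 4: simulation.** There were 3,000 trials per scenario, with two arms of 270 and batch balanced between arms. The chi-square was compared with a logistic model containing eight batch indicators, one prognostic covariate and one pure-noise covariate. Power in the adjusted column is for the model's treatment coefficient.

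| Control-arm R² | Power, chi-square | Power, adjusted | SD of risk difference, raw → standardized | SE of log odds ratio, raw → adjusted |
|---|---|---|---|---|
| 0 | 78.8% | 78.6% | 0.03468 → 0.03463 | 0.2213 → 0.2239 |
| 0.017 | 78.6% | 79.5% | 0.03388 → 0.03369 | 0.2213 → 0.2264 |
| 0.042 | 78.2% | 80.3% | 0.03467 → 0.03397 | 0.2214 → 0.2306 |
| 0.125 | 79.2% | 85.6% | 0.03481 → 0.03290 | 0.2210 → 0.2440 |

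Under the null, rejection was 1.3% to 2.2% adjusted and 1.5% to 1.9% unadjusted. The nominal rate is 1.7%, with simulation error of about √(0.017 × 0.983/3000) = 0.24 points. A further simulation, testing the standardized risk difference itself under the Step 3 figures, gave power of about 80% unadjusted and 83% adjusted, with null rejection of 1.8% and 2.0%.

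Two things follow. Uninformative covariates cost almost nothing. The precision gain appears on the return-rate scale, while the standard error of the odds ratio rises with adjustment in every scenario.

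**The case against.** The strongest reply is that nothing is broken. The chi-square is valid under the randomization described, no stratification factor obliges anyone to adjust, and the test matches the power statement. That stands. A reader might infer from 78% against 80% that the trial is underpowered and needs rescuing; the detectable difference of 11.2 points shows that the gap is essentially rounding.

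The benefit also rests on figures found nowhere in the documents. That stands too. Excluding recently screened patients narrows the range of the screening covariate, and imperfect records would weaken it further: the protocol puts the accuracy of its record algorithm at about 80% before chart review.

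A reader might infer that a last-screening date is held for every subject. The abstraction list does not say so, and a patient who is due because never screened has none. A two-level indicator (prior screening on record, or none on record) avoids this, because eligibility review has to look for that history anyway. The Subject Withdrawal section mentions only de-identified demographics as kept for analysis. Data Collection and Management, however, places chart data in REDCap until after publication, so the variables should be exportable.

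Chance imbalance is a weak argument. On the Step 3 figures, the between-arm difference in the share with prior screening has SD √(2 × 0.24/270) = 4.2 points. Multiplied by 16.7 points, this moves the return-rate difference by about 0.7 points, against a standard error of about 3.4. The test's type I error already allows for it.

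**Conclusion.** The point holds as an efficiency improvement. The plan analyses three raw 2×2 tables and prespecifies no use of baseline factors that it already collects. If those factors do not predict return, adjustment gains nothing and loses almost nothing. If they explain 2%, 5% or 10% of outcome variance, it adds about 1, 2 to 3, or 5 points of power at the planned difference. These figures depend on the assumed R², on the 15% control rate and on reporting a marginal risk difference.

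It would be tempting to conclude that precision is available at no cost. The documents do not support that: the gain is unproven, the result becomes model-based, and covariate coding has to be settled in advance. The case for including batch would be stronger if allocation was done within batch, which the Randomization section leaves open.

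**What to change.** Before outcomes are compared by arm, add to the SAP:

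- One logistic regression of kit return within two months, including all randomized subjects and all four arms, adjusted for batch, age and prior CRC screening on record (yes / none on record).
- The covariate forms: batch as eight indicators, a stated form for age, and screening history taken only from the chart review done before randomization, so that every subject is coded.
- For each incentive arm against control, the standardized (marginal) risk difference with robust or delta-method standard errors, tested at 0.017 with a matching confidence interval. The conditional odds ratio should not be the reported effect.
- The unadjusted chi-square reported alongside, with a statement of which of the two is primary.

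The cost is a paragraph of SAP text and a few lines of code, with no new data. The downside is that the result comes from a model with about ten extra parameters rather than from a 2×2 table. If simplicity is preferred for a pilot, the chi-square can stay primary with the adjusted risk difference prespecified as supportive.

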## 2. Objectives

Primary Objective is to assess the effectiveness of financial incentives to increase the response rates to mailed FIT.

Secondary Objective is to further our understanding of the impact of financial incentives on completing mailed FIT.

Primary Study Endpoint ~~will be an increase in~~ **is the** return rate of completed FITs **within 2 months of outreach between the intervention arms when compared to the control arm.**

Secondary Study Endpoints ~~n/a (the secondary objective is qualitative in nature and thus there is no quantitative endpoint)~~ **include the return rate of completed FITs within 6 months of outreach, the percentage of FIT results that are positive, and the percentage of those positive subjects that receive diagnostic colonoscopy. We will look at rates of participation in FIT or colonoscopy that occur outside the study setting during the study period as an exploratory outcome. We will also evaluate the results of the qualitative survey.**

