## 4 Study Design

### Design

A single center 4-arm randomized pilot study to assess if the rate of completion of FIT is increased by the addition of financial incentives. Potentially eligible subjects will be identified via a data abstraction by Penn Data Store. We will randomly select patients and conduct an electronic medical record (EMR) review using PennChart to confirm eligibility. We will then randomize 1,080 of remaining eligible patients to one of four arms during the intervention phase.

5. Arm 1: mailed FIT kit ~~(usual care)~~ **(control)**

6. Arm 2: mailed FIT kit + \$10 gift card included in mailing (~~reciprocity~~) (**unconditional incentive**)
7. Arm 3: mailed FIT kit + guarantee of receiving a \$10 gift card if kit is returned within two months (~~loss-aversion~~) (**conditional incentive**)
8. Arm 4: mailed FIT kit + entry in a 1/10 chance lottery to receive \$100 gift card if kit is returned within two months (lottery **incentive**)

All 1,080 subjects will receive the mailed FIT kit. Subjects whose FIT results are not recorded in PennChart will receive a follow-up phone call via Interactive Voice Response (IVR) three weeks after the kit was mailed to the subject. Subjects whose FIT results are not recorded in PennChart will receive a follow-up mailed reminder six weeks after the kit was mailed to the subject. Subjects will receive follow-up regardless of the arm to which they are randomized.

A random subsample of 200 subjects will be called twelve weeks after the kit was mailed to the subject to complete a questionnaire. Verbal consent will be obtained from this subsample. This phone call will occur after the intervention and follow-up phases are completed. Analysis will occur after the subsample questionnaire phase is completed.

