### Follow Up Phase

Follow-up is the same for all subjects regardless of the arm to which subjects are randomized. Subjects who have not returned kit 3 weeks ( $\pm 3$  days) after FIT mailing will be contacted using Interactive Voice Response (IVR) to be reminded to complete the kit. Subjects who have not returned kit at least 6 weeks ( $\pm 3$  days) after FIT mailing (and 3 weeks after IVR phone call reminder) will receive a reminder letter in the mail reminding them to complete the kit. We will also conduct a 6-month follow-up via automated chart audit to see if CRC screening was received by participants.

When a negative result is reported, the primary care physician will be notified via PennChart. If the subject utilizes MyPennMedicine, he/she will be sent a message via MyPennMedicine to communicate the negative results. **If the subject does not utilize MyPennMedicine, he/she will receive a letter informing him/her about the negative results.**

When a positive result is reported, the study team will notify the primary care physician and request a colonoscopy referral to the GI department, obtain an order number for a colonoscopy, and then schedule the colonoscopy with the subject and the GI department over the phone.

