### Sub-Sample Questionnaire Phase

A random subsample of 200 subjects will be selected to complete a questionnaire 9 weeks ( $\pm 3$  days) after they received the mailing. Verbal consent will be obtained from this subsample before the questionnaire is administered. Through this questionnaire, the subjects will be asked to confirm their eligibility (e.g. that they had not had CRC screening within the United States Preventive Services Task Force (USPSTF) CRC screening guidelines) and provide additional demographic and socioeconomic status information so that we can better understand what populations, if any, may be more likely impacted by the financial incentives when engaging in CRC screening. We anticipate these questionnaires to take 15-30 minutes to complete over the phone. The research staff will make no more than three attempts to speak directly with the subject. Based on the Penn Family Care quality improvement initiative where we reached about 50% of patients via phone call, we anticipate reaching approximately 100 subjects to complete this sub-sample questionnaire.

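### The stated analysis date and the 23-month duration both fall before the last-mailed subjects reach 6 months, so the timing text conflicts with the 6-month FIT-return endpoint

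*Supplement*

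**What the plan says.** **Endpoint.** In the final protocol, Objectives, the secondary endpoints now "include the return rate of completed FITs within 6 months of outreach". The Follow Up Phase section gives the data source: "We will also conduct a 6-month follow-up via automated chart audit to see if CRC screening was received by participants".

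**Analysis date.** The Data Analysis section, in the final protocol and identically in the final SAP, states: "Analysis will be conducted by the research team twelve weeks after the last subsample questionnaire is completed". The Design section adds: "Analysis will occur after the subsample questionnaire phase is completed". Neither makes the 6-month audit a condition.

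**Questionnaire date.** The Sub-Sample Questionnaire Phase section has "A random subsample of 200 subjects will be selected to complete a questionnaire 9 weeks" (±3 days) after the mailing is received, and the schedule table also puts it at week 9. The Design section instead has "A random subsample of 200 subjects will be called twelve weeks after the kit was mailed to the subject to complete a questionnaire".

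**Duration.** Nine batches of two months each are followed by "a two-month wait period (after the last kit is mailed), and a three month analysis period", for an anticipated total of 23 months. The Study Intervention Phase section likewise spreads mailing over about 18 months.

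No section gives a separate date for the 6-month analysis, or a rule for subjects observed for less than 6 months.

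**The concern.** An endpoint defined over 6 months from outreach can be read for everyone only once the last-mailed subject has passed 6 months. Every dated statement in the plan places analysis, or the end of the study, before that. The 6-month return rate became a named secondary endpoint in the final protocol, but the analysis date and duration do not allow for it.

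If the dates were followed literally and all randomized subjects kept in the denominator, a kit from a late-mailed subject returned after the cut but before 6 months would be missed. The reported rate would then mix full and shortened windows and would not quite be the quantity the protocol names. The cut would also depend on when the last questionnaire call happened to be completed, which has nothing to do with the endpoint.

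**Working it through.** **Inputs.** Mailing period: 9 × 2 = 18 months (Duration). Wait: 2 months. Analysis period: 3 months. Randomized: 1,080. Questionnaire: week 9 (Sub-Sample Questionnaire Phase and schedule table) or week 12 (Design). Analysis: 12 weeks after the last questionnaire (Data Analysis). Endpoint window: 6 months, which is 6 × 365.25 / 12 / 7 = 26.1 weeks.

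**Step 1: the plan's own figure.** 9 × 2 + 2 + 3 = 23 months. This reproduces exactly, so the sum is not in error. What it omits is the 6-month window.

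**Step 2: the SAP date.** This assumes that the last questionnaire subject is in the last mailing and is called on schedule.

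| Questionnaire at | Analysis at | In months | Short of 26.1 weeks by |
|---|---|---|---|
| week 9 | 9 + 12 = week 21 | 4.8 | 5.1 weeks |
| week 12 | 12 + 12 = week 24 | 5.5 | 2.1 weeks |

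Allowing ±3 days moves these to weeks 20.6–21.4 and 23.6–24.4. Neither range reaches 26.1.

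**Step 3: the 23-month calendar.** Last kit: month 18. Analysis begins: 18 + 2 = month 20. Study ends: month 23. Last subject reaches 6 months: 18 + 6 = month 24, one month after the end. The SAP dates fall at about 18 + 4.8 = month 22.8 and 18 + 5.5 = month 23.5, so the two timetables agree to within a few weeks, and both are short.

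**Step 4: how many subjects.** Even mailing is an assumption; it gives 1,080 / 18 = 60 a month, or about 13.8 a week (60 / 4.348 weeks per month).
- Analysis at week 21: 5.1 × 13.8 ≈ 70 subjects (6.5%).
- Analysis at week 24: 2.1 × 13.8 ≈ 29 subjects (2.7%).
- Cut at month 23: 1 × 60 = 60 subjects (5.6%).

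Each batch holds 1,080 / 9 = 120 subjects. If mailing clusters within the last batch, the SAP-rule count could lie anywhere from near 0 to 120.

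**Step 5: what that does to the rate.** The documents give no rate of late return. As an illustration only, suppose 1% to 5% of 70 short-followed subjects returned a kit after the cut but within 6 months. That is 0.7 to 3.5 kits, or about 0.06 to 0.3 percentage points of 1,080.

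**Step 6: what would fit.** Under the same assumptions, the wait after the last questionnaire would have to be at least 26.1 − 9 = 17.1 weeks, or 26.1 − 12 = 14.1 weeks, instead of 12. In calendar terms, 6-month follow-up ends at month 24. If the full analysis period comes after it, 18 + 6 + 3 = 27 months.

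**The case against.** The strongest reply is that the twelve-week sentence dates only the arm-versus-control chi-square analysis, while the Follow Up Phase section separately commits to "We will also conduct a 6-month follow-up via automated chart audit" without exempting late-mailed subjects. On that reading the audit would be completed for everyone and reported later. Part of this stands: no section fixes a data cut for the 6-month endpoint or scores unfinished follow-up as non-return, so it is not established that late subjects would be miscounted. But the sentence is unqualified, the Design section likewise ties analysis to the questionnaire phase alone, and no later date appears anywhere.

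The 23 months are only anticipated, and calls may run late because up to three attempts are allowed. A slip of about two weeks would close the gap on the 12-week timing; the 9-week timing needs about five. In the other direction, the subsample is a random 200 of 1,080, so the last person called may have been mailed before the final kits, which would widen the gap.

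A reader might also infer more than the documents support:
- **That 22% of subjects are affected.** Everyone mailed after month 14 would be short if data were frozen when analysis begins at month 20: 4 × 60 = 240. Nothing says data are frozen then, and the SAP rule gives a date near month 23.
- **That the colonoscopy percentage is biased against its definition.** The 6-month window is attached only to FIT return. Colonoscopy after a positive result has no stated window, which is a different matter.
- **That the arms are compared unfairly.** Planned follow-up is the same in all arms, so no between-arm bias is shown.

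**Conclusion.** The conflict is real: followed as written, the analysis date and the duration cannot deliver 6-month FIT return for the last-mailed subjects. It holds on either questionnaire timing, and it is an inconsistency of timing, not a faulty sum.

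The effect is modest. The counts in step 4 rest on even mailing and an on-schedule last call, and the consequence is a slight under-count of 6-month returns if the dates are applied literally. The 2-month primary endpoint is complete on every timetable in the plan. The point should be corrected because the correction is cheap; it does not threaten the trial's main conclusion.

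**What to change.** 1. In the SAP, set the data cut for the 6-month FIT-return endpoint no earlier than 6 months after the last mailing, plus a short stated lag for charting.
2. State that the twelve-week rule applies to the 2-month primary analysis, which can keep its current schedule.
3. Restate the study duration to match: at least 24 months, and up to about 27 if the full three-month analysis period follows the cut.
4. Reconcile the 9-week and 12-week questionnaire timings, since the analysis date depends on them.

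The cost is a change of wording in the protocol and SAP and a delay of a few months for the secondary results. The chart audit is already planned and automated, so no extra subjects or procedures are needed.
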